### Sample size calculation

The sample size was calculated separately for both study parts. For part I, we assumed that the expected cfPWV corresponded to 8.5, 9.5, and 11.5 m/s for HOA, HOS and OSR, respectively, and that the standard deviation was 1.5 m/s (Tedesco et al., 2004; Gando et al., 2010). With a 2-sided significance level of 0.05, the sample size needed to attain a targeted power of 80% for detecting a difference with magnitude 1.0 m/s was 36 participants per group (the comparison between HOA and HOS) and for detecting a difference with magnitude 2.0 m/s, it was 10 participants per group (the comparison between OSR and HOS). For part II, we assumed that the expected difference in cfPWV after 12 weeks between OSR in the intervention and those in the control group was 1.0 m/s and that the standard deviation was 1.5 m/s (Madden et al., 2009). By including the baseline cfPWV (before the start of the intervention period) as a covariate in the pre-specified analysis, we will further reduce error variability and therefore assumed that the correlation between baseline and outcome cfPWV was 0.3. With a 2-sided significance level of 0.05, the sample needed to attain a targeted power of 80% for showing superiority of the intervention over control was 34 participants per group. Taking dropouts into account, we plan to include a total of 40 HOA, 40 HOS and 80 OSR. The POWER and GLMPOWER procedures in SAS 9.3 (SAS Institute Inc., Cary, NC, USA) were used for sample size calculation for the first and second study part, respectively.

### Exercise intervention and control condition

#### High intensive interval training (HIIT)

The exercise intervention for the OSR intervention group is a supervised Nordic-Walking training three times a week with gradually increased intensity during the first 2 weeks. In the first week, we will teach Nordic Walking technique, warm-up and cool-down elements as well as continuous walking training with moderate intensity at 75% of maximal heart rate (HRmax). In the second week, the intensity will increase to 80–90% of HRmax. In the following 10 weeks, HIIT will be performed as described below. Exercise scientists will supervise all training sessions.

The following protocol will be used (modified from Wisloff et al., 2007):

Three supervised trainings per weekIntensity: 10 min warm-up at 65-70% HRmax, 4x4 min interval training at 80-90% HRmax with 3 min of active recovery at 65-70% HRmax, 10 min cool down at 60-70% HRmaxDuration: 45 min

#### Control group (CG)

The control group is asked to orientate their physical activity according to the European Guidelines on vascular disease prevention in clinical practice (Backer et al., 2003).

## Imaging methods and course of measurements

### Macrovascular aging

#### Central pulse wave velocity

Carotid-femoral PWV (cfPWV), the gold standard for the measurement of arterial stiffness, is assessed by using a SphygmoCor® device (AtCor, Medical Pty Ltd, Sydney, Australia). The good intra- and interobserver reproducibility of this technique has been demonstrated in healthy populations and in patients with chronic kidney disease (Frimodt-Møller et al., 2006, 2008). After 10 min of rest, pulse waves are recorded using a high-fidelity tonometric transducer at two sites (right carotid artery and right femoral artery). Pulse wave travel distance is determined by subtracting the distance between the manubrium to the carotid artery from the distance between the femoral artery to the manubrium as previously described (Townsend et al., 2015). cfPWV measurements are considered to meet the quality control parameters if two consecutive measurements are visually acceptable and within 1 m/s of each other with a standard deviation of <10% (Sigrist et al., 2010). If this criterium could not be reached a third measurement was applied. The mean of all valid measurements represents the cfPWV value.

#### Peripheral pulse wave velocity

Femoral-tibial PWV (ftPWV) is assessed by using the same SphygmoCor® device as for central PWV. Peripheral PWV is determined as the travel time of the pulse wave between the two recording sites at the femoral artery and the posterior tibial artery divided by the distance between the two recording sites. All other procedures and conditions are the same as for central PWV (see above).

#### Pulse wave reflection (PWA)

AIx and AIx@75 are measured using the gold standard device for single measurements (SphygmoCor®). The augmentation index from the central pulse is calculated as: AIx = 100 × (P2 – P1)/pulse pressure, where P2 is the peak of the reflected backward wave, P1 is the peak of the forward pressure wave and central pulse pressure is the systolic pressure maximum minus the diastolic pressure. A positive AIx would indicate an augmentation of peak systolic pressure by the reflected wave. Pulse waveform is obtained using applanation tonometry (SphygmoCor® device, ATCor Medical, Sydney, Australia) on the right radial artery. Ten-second recordings are accumulated until either two analyses with a quality index of ≥90% or three of ≥80% were available. By applying a generalized transfer functions (GTF) the central arterial pulse waveform is estimated by the SphygmoCor® software. These transfer functions have been validated previously during rest (Gallagher et al., 2004) and exercise (Sharman et al., 2006). The calculated central arterial pulse waveform is subjected to further analysis, such as the determination of AIx and AIx@75. Reproducibility has been shown to be acceptable at rest (Filipovský et al., 2000) and during exercise (Holland et al., 2008).

#### 24-h ambulatory monitoring of central hemodynamics

Twenty-four hours ambulatory pulse wave monitoring is obtained using an oscillometric Mobil-O-Graph® 24 h PWA Monitor device (I.E.M GmbH, Germany) with integrated ARCSolver® software. Based on the oscillometric data, central hemodynamics as well as the 24-h PWV is calculated. Oscillometric pulse wave analysis are performed every 20 min for 24 h. Subjects are instructed to hold their arm as steady as possible during the measurements but otherwise maintain their daily routine with no additional physical activity while wearing the device. After data readout, every individual measurement is reviewed for erroneous values. Values are deleted if the quality of data is graded 3 or 4 by the ARCSolver® software. The methods used for these analyses are the same as used by the SphygmoCor® software described previously (Wassertheurer et al., 2010). Validity and reproducibility of oscillometric estimates of cPP, Aix, and AIx@75 are comparable with laboratory settings (Wassertheurer et al., 2010; Luzardo et al., 2012; Papaioannou et al., 2013).

#### Intima media thickness (IMT)

For the semi-automatic evaluation of intima-media thickness (IMT), B-Mode clips are conducted using an ultrasonic device UF-870AG (Fukuda Denshi, Japan) according to current guidelines (Touboul et al., 2012). With the participant in supine position and the head rotated by 45° either to the left or right side two locations on both sides are scanned. Ear-to-ear and horizontal clips are recorded over at least three heart cycles using the US machines inbuilt 3-lead ecg function. Post procession and video-based IMT-admeasurement of the exported clips is performed using the Dynamic Artery Analysis software (DYARA) as described elsewhere (Teynor et al., 2012), using image averaging over three heart cycles. Reproducibility of the aforementioned method is excellent (Touboul et al., 2012).

### Microvascular aging

#### Static retinal vessel analysis (SVA)

The retinal microcirculation is easily accessible by using the Retinal Vessel Analyser (RVA, IMEDOS Systems, Jena, Germany) and a fundus camera (450 FF; Carl Zeiss, Jena, Germany). The technique allows for the analysis of the structure and function of retinal arterioles and venules. To measure retinal vessel diameters, we analyze three valid pictures from one eye with an angle of 50° and the optic disc in the center. The detailed procedure is described elsewhere (Hanssen et al., 2011). Briefly, retinal arterioles and venules, coursing through an area of 0.5–1 disc-diameter from the optic disc margin, will be identified semi-automatically at higher magnification using special analyzing software (Vesselmap 2, Visualis, Imedos Systems UG). Diameters will be averaged to central retinal arteriolar (CRAE) and venular (CRVE) equivalents, and the arteriolar-to-venular-ratio (AVR) will be calculated from the CRAE and CRVE. The inter-observer and intra-observer interclass correlation coefficient for the measurement of retinal vessel diameters ranges from 0.75 to 0.99 (Hubbard et al., 1999; Wong et al., 2004b).

#### Dynamic retinal vessel analysis (DVA)

Functional retinal vessel analysis requires pharmacological dilatation of one pupil with conventional eye drops (Tropicamide 0.5%). Microvascular function is analyzed by a flicker-induced dilatation of retinal arterioles and veins. We use a fundus camera (450 FF; Carl Zeiss, Jena, Germany), with a charge-coupled device for electronic online imaging and a personal computer for system control, analysis and recording of the obtained data, allowing non-invasive assessment of retinal endothelial function mediated by neurovascular coupling following flicker stimulation (Falsini et al., 2002; Polak et al., 2002). The whole procedure is described elsewhere (Nagel et al., 2004; Gugleta et al., 2006; Garhofer et al., 2010). Due to the described inter- and intra-individual variations of vessel diameters (Hubbard et al., 1999), the mean diameter resulting from three baseline measurements before application of the stimulus in each of three flicker cycles is defined as 100%. The ensuing vessel diameter changes are recalculated in % to this individual baseline value (Pemp et al., 2009). From the median of the three curves, parameters such as maximal vessel dilatation, maximal reactive vessel constriction and area under the reaction curve during and after flicker stimulation can be analyzed (Kotliar et al., 2011).

#### Cardiac aging

Echocardiographic parameters are assessed using an ultrasonic device (UF 870AG, Fukuda Denshi, Japan) according to current guidelines (Nagueh et al., 2009; Lang et al., 2015). Briefly, global systolic function is described by ejection fraction based on chamber quantifications as recommended. Linear method and 2D based formulas are used to calculate left ventricular function mass. Right ventricular measurements (such as tricuspid annular plane systolic excursion) as well as atrial volume measurements give further insight into mechanical properties of the heart. Diastolic function is assessed using mitral inflow patterns (E, A, deceleration time, intraventricular relaxation time), tissue Doppler derived mitral annular velocities (E′, A′) and pulmonary artery pressures. Additionally, speckle tracking echocardiography is used to calculate strain.

#### Autonomic aging

We record a 12-lead-ECG for 20 min in supine position before and 10 min after a treadmill test using Custo Diagnostic Software (Custo Med GmbH, Germany). The additional post-treadmill assessment will enable us to evaluate recovery of HRV after acute bouts of exhaustive exercise. Raw data are extracted and processed to derive HRV parameters. Time-domain parameters are standard deviation of normal to normal (NN) RR intervals (SDNN), root mean square of successive differences (RMSSD) and the number of pairs of successive NNs that differ by more than 50 ms (NN50). Frequency-domain paramters include high- and low frequency power. Additionally, Heart Rate Turbulence (HRT) and Deceleration Capacity (DC) are calculated (Schmidt et al., 1999; Bauer et al., 2006).

#### Inflamm-aging and circulating CV risk factors

To analyse the influence of physical activity on immunological processes and the association of inflammation, blood samples are taken. They are drawn by venepuncture of the cubital fossa of the right or left arm by trained medical staff in a fasting state. The blood is transported directly to the clinical chemistry laboratory for further analysis or centrifuged and put on ice. Clinical routine measurements including total blood count, total cholesterol (TC), low- (LDL) and high-density lipoprotein (HDL), triglyzerides (TGA) (colorimetric tests) as well as fasting glucose levels (hexokinase reference method) and insulin levels (automated immunoanalyzer system) to estimate insulin resistance (by HOMA Score) are measured. Samples, which are not analyzed directly, will centrifuged and the plasma aliquots will be frozen at a temperature of −80°. To analyse plasma concentration of the following specific biomarkers blood samples will be defrosted and processed. Cytokine-specific ELISA kits will use to analyse inflammatory serum biomarker interleukin 6 (IL 6), 10 (IL-10), and tumor necrosis factor alpha (TNF-α) according to the manufactures instructions (IL-6/-10: Bender Med-Systems (eBioscience), Austria; TNF-α: Bio-source, USA). The samples will be distributed in duplicates on the plates and the intra-assay and inter-assay coefficient of variation need to be ≤ 10%. High-sensitive c-reactive protein (hsCRP) will be analyzed by immunoturbidimetric latex CRP assay (Cobas 8000, Roche-Diagnostics, Basel).

#### Physical fitness, physical activity, and anthropometry

Physical fitness will be assessed by performing an individualized ramp protocol on the treadmill. We will measure peak oxygen uptake (VO2peak) and maximal heart rate (HRmax). The individualized design with increasing speed and ramp steepness will be used to reach volitional exhaustion after approximately 10 min for every participant. The calculation of this protocol is based on the subject's age and estimated peak metabolic equivalent units (METS) as previously recommended (Bader et al., 1999; Myers and Bellin, 2000). The ECG will be monitored by medical personal during the whole test. Blood pressure will be measured during, immediately after and 3 min after the exercise test. Every minute Ratings of Perceived Exertion (RPE) will be requested (Borg, 1982). Ventilatory parameters, including VO2max and heart rate, will be measured by using the Cortex Metalyzer® 3B metabolic test system (Cortex Biophysik GmbH, Leipzig, Germany).

All participants will get an accelerometer (Aipermon GmbH, Germany) to analyse their physical activity (PA). They have to wear the device on their left hip for the whole day on six consecutive days. Raw data will be copied onto a computer and the data will be viewed using the ActiCoach MPAT2Viewer (Aipermon, GmbH, Germany). The following parameters can be analyzed by this software: total time (minutes per day) spent passively (PAS), actively (ACT), walking (WLK), and fast walking (FWLK). Walking and fast walking times will be joined to a total walking time (TWT). We have previously validated activity modes and accelerometer detection precision (Jehn et al., 2009a,b, 2010, 2011).

Self-reported PA will be measured with the Freiburg Questionnaire of physical activity. The questionnaire interrogates health-related physical activities using self-reported activities within the last week/month. It creates reliable and valid values of PA and inactivity (Frey et al., 1999). The total PA is expressed in hours per week. The Ainsworth Compendium in metabolic equivalents (METS) estimates the intensities. The formula to calculate the energy expenditure per week is described elsewhere (Ainsworth et al., 1993).

Anthropometric data will be measured in a fasting state in the morning. The Inbody 720® (JP Global Markets GmbH, Germany) device will be used to obtain weight, BMI, skeletal muscle mass and body fat (Anderson et al., 2012). Height and waist circumference will be measured by using a normal measuring tape with respect to current guidelines.

#### Potential pitfalls

Our main outcome (cfPWV) as well as most other vascular measurements are affected by age, hemodynamic variability, lifestyle behavior, and circadian fluctuations. To minimize external interference and variability, several measures are considered. Groups are matched for age and sex. Standardized vascular imaging is performed under fasting conditions in the morning after 10 min of rest in a supine position. Participants are encouraged to refrain from alcohol, caffeine and if applicable from smoking 12 h prior to the examinations. Exercise and vigorous physical activity should not be performed 24 h before the visits. The OSR group is allowed to take their medication in the morning. These measures help to minimize intra-individual as well as within-day variability.

Change of medication or start of a structured diet during the 12 week-week intervention or control condition are indications for exclusion. In addition, the start of structured exercise in the control group is considered an exclusion criterion. To prevent the start of exercise in the control group, all participants of this group are invited to take part in the voluntary supervised exercise program after the post measurements. To prevent high drop-out rates and optimize adherence to the exercise regime, every exercise session starts with strength, mobilization and coordination exercises and includes a warm-up and a cool-down. The first 2 weeks of the exercise program focus on technical and coordinative skills at lower intensities before HIIT is started in the third week into the program.

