### Hypotheses

Hypothesis 1 (Part I): cfPWV is lower in HOA compared to HOS

Hypothesis 2 (Part I): cfPWV is higher in OSR compared to HOS

Hypothesis 3 (Part II): cfPWV in OSR can be reduced by 12 weeks of HIIT compared to controls.

The same hypotheses will be addressed for the secondary and further outcomes.

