### Study procedures and ethical considerations

All participants are briefed verbally and receive information approved by the Ethics Committee of Northwestern and Central Switzerland (EKNZ) giving details on the study procedures, the RCT and the process of randomization. The study will be carried out in accordance to the protocol and with the principles stated in the Declaration of Helsinki and the Guidelines of Good Clinical Practice (GCP) (World Medical Association, 2013). This study protocol was design according the SPIRIT Guidelines.

All measurements and procedures applied in this study are non-invasive. Routine exercise ECG includes an exertional stress test as a medical necessity and safety precaution to evaluate cardiorespiratory health in all subjects. The OSR group undergoes a high intensity walking-based training program. HIIT has previously been applied in a wide range of patients including patients with coronary artery disease. The risk for cardiovascular events has been proven to be equally low for both HIIT and moderate continuous intervention strategies (Rognmo et al., 2012). Retinal vessel analysis includes mydriasis of one eye. Using a mydriaticum (Tropicamid 0.5%), the pupils are dilated and enable retinal vessel analysis. The eye drops can cause temporary discomfort, oftentimes a burning sensation for 1–2 min. Flickerlight exposure can potentially cause slight headaches. The collaborating ophthalmology department in Basel will offer back up at all times in the unlikely event of continuous discomfort.

All participants are committed to sign a consent form and will be informed about their right to withdraw from the study without any consequences. A study assistant will randomize the OSR group in an intervention or a control group by drawing a lot after the last pre-intervention assessment. Participants and investigators are blinded for the group membership during the pre-measurements. All participants are to be recruited from our outpatient department, the Metabolism Unit of the University Hospital Basel, Basel, Switzerland and, in addition, with postings on University webpages and advertisements in local newspapers. We aim to recruit the HOA group in running clubs and on running events in and around Basel. A total of 160 participants will be recruited for the study.

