**Figure 3 F3:**
[figure not shown]
Principle concept of the systems physiology approach.

The ExAMIN AGE Study resembles new approaches in the structural and functional diagnostics of aging processes including systems such as the vasculature, the heart, autonomic function and inflammation. The results have a focus on vascular imaging and on the non-pharmaceutical treatment of vascular health in older inactive individuals at risk. The integrative approach will help to determine the best non-invasive means to diagnose and define cardiovascular risk in advanced age and disease. This study design allows the examination of pathophysiological links between small and large arteries, the so called “vascular coupling” or “arterial cross-talk.” To date little is known about the interaction between the two vascular beds and how they affect each other. It also enables to examine the cross-talk between the vasculature and the heart. Exercise interventions can improve both entities and play a key role in the treatment of cardiovascular and metabolic diseases.

Our study has some limitations. We are aware that the recruitment of healthy older sedentary individuals (HOS) is challenging. It needs to be ascertained that all three groups are strictly matched for age. The analysis of the association of physical fitness with cardiovascular health and aging processes in the three groups represents a cross-sectional approach and is not based on prospective longitudinal data. Life-long activity is analyzed by subjective reporting but is supported by objective analysis using accelerometry and spiroergometry. The cross-sectional study design does not give evidence of a temporal relationship between physical activity exposure and physiological outcome. However, the interventional part of the study, where participants are randomly allocated to the intervention or the control group, allows for a causal and temporal analysis of the improvement of aging processes in individuals at risk. The extensive phenotyping of vascular health and other physiological systems as well as the analysis of the impact of HIIT are the main strengths and innovations of the study.

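### Part II excludes already randomised participants for events during the 12 weeks, one rule for controls only; unless they are still measured and analysed as allocated, the randomised comparison is compromised

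*Protocol article*

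**What the plan says.** Randomisation of the OSR group takes place "by drawing a lot after the last pre-intervention assessment" (Study procedures and ethical considerations). The Study design section agrees: it follows the three baseline visits and precedes the 12-week period.

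The Potential pitfalls section then sets two rules for that period:

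- Both arms: "Change of medication or start of a structured diet during the 12 week-week intervention or control condition are indications for exclusion".
- Control arm only: "the start of structured exercise in the control group is considered an exclusion criterion".

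Other statements that bear on these rules:

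- Control condition: "The control group is asked to orientate their physical activity according to the European Guidelines on vascular disease prevention in clinical practice" (Control group).
- Hypothesis 3: "cfPWV in OSR can be reduced by 12 weeks of HIIT compared to controls" (Hypotheses).
- Analysis: analysis of covariance of week-12 carotid-femoral pulse wave velocity (cfPWV), adjusted for baseline, between the two OSR arms (Statistical analysis). No analysis set is named.
- Blinding: "Participants and investigators are blinded for the group membership during the pre-measurements" (Study procedures and ethical considerations). None is described for the 12 weeks that follow.
- Losses: "Taking dropouts into account, we plan to include a total of 40 HOA, 40 HOS and 80 OSR" (Sample size calculation).
- Interpretation: because allocation is random, Part II "allows for a causal and temporal analysis of the improvement of aging processes in individuals at risk" (Discussion and conclusion).

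**The concern.** By their own wording, the two rules concern events after randomisation. They are not eligibility criteria, which have a separate section. Three features make them a risk to the primary contrast of Part II.

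1. **The events can depend on the arm.** Medication or diet may change because of how the 12 weeks go, and that can differ between trained and untrained participants. Selecting on such events breaks the balance that randomisation created.
2. **One rule is one-sided.** Only a control can be excluded for starting structured exercise. No matching rule covers HIIT participants who train outside the programme.
3. **The decision is unprotected.** The article does not say who decides on an exclusion or whether that person knows the allocation, and the stated blinding covers only the baseline measurements.

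At stake is an estimate that is presented as causal on the strength of randomisation but may be computed on groups that are no longer those randomised. More recruitment restores lost power but does not remove this bias.

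**Working it through.** **Step 1. Reproduce the plan's own figure.** Inputs from Sample size calculation: difference 1.0 m/s, SD 1.5 m/s, baseline–outcome correlation 0.3, two-sided 0.05, power 80%.

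- Residual SD = 1.5 × √(1 − 0.3²) = 1.431 m/s.
- Normal approximation: n = 2 × (1.960 + 0.842)² × 1.431² / 1.0² = 32.1, so 33 per arm.
- Noncentral t with one covariate (error df = 2n − 3): power is 79.8% at n = 33 and 81.0% at n = 34.

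The stated 34 per arm is reproduced. With 40 per arm recruited, the implied allowance for all losses is 1 − 34/40 = 15%.

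**Step 2. Order of events.** Baseline visits, then the lot, then 12 weeks in which the exclusion rules apply, then the week-12 assessment. Every exclusion under these rules is therefore after allocation.

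**Step 3. Size of a possible bias.** Let q be the share of one arm excluded, and d the difference in mean week-12 cfPWV (baseline-adjusted) between those excluded and those retained. The mean of the retained participants differs from the mean of the full arm by q × d, and the contrast shifts by the same amount. The article gives neither q nor d, so both are assumptions:

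| q | d (m/s) | shift q × d (m/s) | share of the planned 1.0 m/s |
|---|---|---|---|
| 10% | 0.5 | 0.05 | 5% |
| 10% | 1.0 | 0.10 | 10% |
| 20% | 0.5 | 0.10 | 10% |
| 20% | 1.0 | 0.20 | 20% |

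**Step 4. Effect on type I error, with 34 analysed per arm.** Standard error = 1.431 × √(2/34) = 0.347 m/s; error df = 65; critical t = 1.997. If the true effect is zero, the noncentrality is shift / 0.347:

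- shift 0.05: 0.144, type I error 5.2%;
- shift 0.10: 0.288, type I error 5.9%;
- shift 0.20: 0.576, type I error 8.8%.

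**Step 5. Direction.** Hypothesis 3 supposes that exercise lowers cfPWV. On that premise, controls who start structured exercise tend to have lower week-12 values. Removing them raises the control mean, which favours HIIT. The medication and diet rules have no such presumption, and shifts in the two arms can add or cancel.

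**Step 6. Power, as a side issue.** On the plan's inputs, power is 87.0% with 40 per arm, 81.0% with 34, 78.6% with 32, 75.8% with 30 and 72.8% with 28. It falls below 80% only when total loss exceeds about 15%, and even 20% loss (32 per arm) costs little.

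**The case against.** The strongest reply is that the article does not say what exclusion means. It could mean leaving the programme, missing the week-12 visit or leaving the analysis. The statistical section names no restricted set, and Study design says that the baseline assessments are repeated at 12 weeks. A full protocol or analysis plan may define the analysis population, and an article may leave that to it. This stands in part. A reader might infer that the analysed groups certainly differ from the randomised ones, and the text does not support that. The point is conditional. But it rests on a rule the article states, not on a missing definition. A later as-randomised analysis would conflict with that rule, or would lack week-12 values for participants already excluded.

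A reader might also infer that the control advice and the exercise criterion contradict each other outright. They do not. The criterion concerns structured exercise, while the control condition is described as general recommendations for daily activity. A control who answers that advice with structured exercise would meet the criterion, so the passages need to be reconciled, but the tension goes no further.

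Nor is the one-sidedness wrong in itself, since structured exercise is what the HIIT arm is assigned. Controls are also offered the supervised programme after the final measurements, which should reduce how often the rule is triggered.

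Finally, a firm claim that the HIIT benefit is inflated would go too far. Controls might start exercising because their health is worsening, and removing them would then act the other way.

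**Conclusion.** The concern holds in conditional form. The article directs that randomised OSR participants be excluded for events during follow-up, with one rule for controls only. It provides neither for their week-12 measurement nor for their analysis as allocated. Followed in that way, the rules would make the Part II contrast one between selected groups and undermine the causal reading.

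The control-only rule would plausibly favour HIIT; the direction of the other rules is open. The shift of 0.05–0.20 m/s, with type I error of about 5.2–8.8% against a nominal 5%, illustrates assumed exclusion shares and outcome differences and is not an estimate for this trial. The sample size is not in dispute, and power is a minor consequence. The point deserves correction before the rules are applied, because week-12 outcomes that are not collected cannot be recovered.

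**What to change.** Replace the two exclusion sentences under Potential pitfalls with:

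> All randomised OSR participants are invited to the week-12 assessment and are analysed in the arm to which they were allocated (primary analysis). Medication change, start of a structured diet, and structured exercise outside the allocated programme are recorded in both arms as intercurrent events.

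The words *outside the allocated programme* are needed so that the HIIT arm's own training does not count as an event. Keep the restricted set only as a supportive analysis, labelled as a non-randomised comparison. Reconcile the control-group advice with the structured-exercise criterion, so that it is clear what a control may do without meeting that criterion.

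The cost is a change of wording and a few extra week-12 visits. The as-allocated estimate may be slightly diluted by exercise in the control arm.
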